### Blinding

The study medication will be delivered to the skating ring in a standard syringe, containing either 1 mg salbutamol in isotonic saline or solely isotonic saline with a standard label. The lack of inhalation in the control group cannot be masked. Assessment of lung function will be assessed without knowledge of the received treatment.

### Discontinuation

Participants can leave the study at any time for any reason if they wish to do so without any consequences. The investigator can decide to withdraw a participant from the study for urgent medical reasons (for example, a fall in FEV_1_ >25% from baseline). Discontinued participants will not be replaced.

### Data analysis

Best values of spirometric measurements, mean values of FOT measurements and EMG measurements recordings of 60 s during FOT measurements will be used for statistical calculations. Data will consist of a set of comparing participants who nebulized 1 mg Salbutamol, isotonic saline, and one set of controls. Once gathered, data will be analyzed with SPSS analytical software after testing for normality with a Shapiro-Wilk test. Difference between groups will be analyzed with a chi-square test for dichotomous variables and a one-way ANOVA, followed by a post-hoc Tukey’s test for continuous variables.

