### Outcomes

The primary outcome of the study is the difference in percentage fall in FEV_1_ from baseline after exercise in the different treatment groups. Secondary outcomes of the study are the difference in airway resistance and reactance in kPa/l/s at low frequency as measured with the FOT and difference in diaphragm and intercostal muscle activity in the logarithm of mean bottom ratio of respiratory muscle activity between the different treatment groups.

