### Sample size

Numbers of study participants were calculated using the calculations of Dupont, and setting power of the study at 80% and *P*=0.05 [16]. Data used to produce these numbers came from research performed by Driessen *et al.*[17]. We expect no difference between placebo and control groups. Analyzing the protective effect of salbutamol in a randomized control trial, with an expected difference in FEV_1_ of 10% and a standard deviation from the mean of 6% the number of participants was set at 13 per group. Therefore the total number of randomized participants will be at least 39. In the aforementioned research performed by Driessen *et al.*, 95% of patients completed the study. Therefore the enrolled patient count will be 1.05 times the total number (39•1.05=41).

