### Randomization

Participants are randomized using a pre-generated randomization list. For randomization a linear congruential algorithm of Park and Miller with Bays-Durham shuffling was employed, using block sizes of two, four, and eight participants. Stratified minimization will commence using the number of intensive training years (> or <5 years) and the current use of asthma medication. A flow diagram of the progress through the phases of the study can be seen in Figure 1.

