## Trial status

The trial is currently enrolling participants and collects data on three separate dates; all test dates will be official races, approved by the Royal Dutch Skating organization (http://www.knsb.nl). The first test date will be 21 December 2012. The second test date is planned in February 2013. A third test date will be added in the fall of 2013. Data analysis is expected to be completed in December 2013.

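### The one-way ANOVA leaves out the two allocation factors and the pre-race values; adding them is a nearly free gain in precision

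*Protocol article*

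**What the plan says.** Under Data analysis, the protocol article states "Difference between groups will be analyzed with a chi-square test for dichotomous variables and a one-way ANOVA", followed by Tukey's post-hoc test. It names no covariate or stratum.

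Under Randomization it states "Stratified minimization will commence using the number of intensive training years (> or <5 years) and the current use of asthma medication". The same section describes a pre-generated list in blocks of two, four and eight, for a design with three arms.

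Under Pulmonary function measurements, spirometry and FOT are taken before the race and at three times after it. Data analysis adds that EMG is recorded during the FOT measurements.

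Under Outcomes, the primary endpoint is the percentage fall in FEV1 from baseline. The FOT endpoint is the "difference in airway resistance and reactance in kPa/l/s at low frequency as measured with the FOT" between groups, with no statement on whether the pre-race value is used. The EMG endpoint is a log ratio compared between groups, also without mention of the pre-race value.

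Trial status says that the study "collects data on three separate dates". Race date is not named as an allocation factor.

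**The concern.** Choosing training years and asthma medication as balancing factors implies that they are thought to predict the response. Balancing removes their contribution from the true sampling variance of a difference between arms. A one-way ANOVA does not know this: it leaves their variance in the error term. The standard error is then larger than the design warrants, intervals are too wide, and the test rejects less often than its nominal level.

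Pre-race values raise a related but different point. They play no part in allocation, so leaving them out does not bias the standard error. It only forgoes precision that the data could give. With 13 participants per arm, precision is worth having.

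**Working it through.** **Inputs from the document (Sample size).** The article works with "setting power of the study at 80% and *P*=0.05", "with an expected difference in FEV_1_ of 10% and a standard deviation from the mean of 6"% and states that "the number of participants was set at 13 per group". Three arms of 13 give 39 participants and 39 − 3 = 36 error degrees of freedom.

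**Assumed inputs.** The share of outcome variance explained by covariates (R²) and the correlation between pre- and post-race FOT are not in the document. Ranges are shown. Tests are taken as two-sided.

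**1. The plan's own figure.** A difference of 10 with SD 6 at 80% power needs 7 per group by a two-sample t test and 9 by Tukey pairwise comparison, not 13. That is a separate matter. What counts here is the power at 13:
- noncentrality = (10/6) × √(13/2) = 4.25
- Tukey critical value = 3.457/√2 = 2.444 on 36 df
- power ≈ 96.0%

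**2. Unadjusted precision.**
- SE of a pairwise difference = 6 × √(2/13) = 2.35 points
- Tukey 95% half-width = 2.444 × 2.353 = 5.75 points

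**3. Type I error when balanced prognostic factors are omitted.** Take 36 participants, 12 per arm, exactly balanced over four equal strata, total variance 1. The between-arm mean square has expectation 1 − R². The one-way error mean square has expectation (1 − R²) + R² × 36/33. The F ratio is therefore deflated by about 0.97/(0.97 + 0.033) = 0.97 at R² = 0.03, 0.90/(0.90 + 0.109) = 0.89 at 0.10, and 0.70/(0.70 + 0.327) = 0.68 at 0.30. Simulated rejection rates of the nominal 5% test (repeat runs differ by about 0.1 point):

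| Variance explained by the two balanced factors | Type I error |
|---|---|
| 3% | about 4.4% |
| 10% | about 3.5% |
| 30% | about 1.3% |

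A covariate left to chance that explains 10% or 30% of the variance leaves the error at about 5%. Only the part belonging to the balanced factors matters.

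**4. Gain and cost of adjustment.** Two binary factors and one baseline use 3 df, leaving 33. The Tukey critical value becomes 3.470/√2 = 2.454. With balanced covariates the half-width is 2.454 × 6 × √(1 − R²) × √(2/13):

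| R² | Half-width (points) | Tukey power for 6 points |
|---|---|---|
| unadjusted | 5.75 | 54.7% |
| 0 | 5.78 | 54.4% |
| 0.10 | 5.48 | 59.6% |
| 0.30 | 4.83 | 72.1% |

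The 6-point effect is illustrative. Adjustment breaks even at R² = 1 − (3.457/3.470)² ≈ 0.008 if all three terms are balanced. If all three were left to chance, the variance is inflated by about 1 + 3/32 = 1.094, and break-even rises to 1 − 0.992/1.094 ≈ 0.09. With race date added (five terms), the corresponding values are 0.014 and 0.15.

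**5. FOT, at an assumed correlation of 0.7 and equal SDs before and after.**
- Against a post-only comparison: √(1 − 0.49) = 0.71, an SE about 29% smaller.
- Against a change score, whose variance is 2 × (1 − 0.7) = 0.60: √(0.51/0.60) = 0.92, an SE about 8% smaller.

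**The case against.** The best defence is that the planned test errs towards caution. It creates no false positives, and on the stated inputs the power is ample. Both statements are true, which is why this is an improvement and not a threat to validity. The article's Discussion does concede that not every skater will show a substantial fall, so a mean effect below 10 points is plausible.

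An analysis plan that is not shown may refine the model. But the article itself names a specific model, and that model does not match its own allocation.

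A reader might infer several stronger points that the document does not support:
- **That the conservatism extends to everything left out.** It applies only to covariates that the allocation balances. If the covariates together explain 10% of the variance and the balanced factors 3 of those 10 points, the type I error is about 4.4%, not 3.5%.
- **That baseline is ignored.** For FEV1 it enters through percentage fall.
- **That the design has already secured the precision from race date.** Race date is not among the allocation factors named.
- **That FOT is compared as raw post-race values.** A change from baseline has the same unit, and the text does not settle which is meant. The 29% figure holds only under the post-only reading.
- **That full balance can be assumed.** Blocks of two, four and eight do not divide evenly over three arms, and the article combines them with minimization, so the balance achieved is uncertain.

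**Conclusion.** The point stands as a nearly free improvement. The stated analysis omits two factors that the allocation balances, and it does not use pre-race values as covariates. If the factors are prognostic and balance holds, the nominal 5% test runs at roughly 4.4% down to 1.3% as their share of variance goes from 3% to 30%. That share is an assumption, and the upper end would require the two binary factors alone to explain 30%. For baseline and race date the loss is precision only.

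The stated power is not at risk. The benefit lies in three places: effects smaller than 10 points; the saline-control comparison, where no difference is expected, so that the interval width of about ±5.75 points decides how informative the result is; and the FOT and EMG outcomes. For FOT the SE gain would be about 8% to 29% at a correlation of 0.7, depending on how the endpoint is read.

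**What to change.** In Data analysis, replace the one-way ANOVA for continuous outcomes with a linear model (ANCOVA) containing treatment, training years (two levels), current asthma medication (yes/no) and the pre-race value of the same measure. Make Tukey-adjusted pairwise comparisons of the adjusted means. Keep the unadjusted ANOVA as a sensitivity analysis. State in Outcomes whether the FOT and EMG endpoints are post-race values or changes from the pre-race value. Race date is optional, since three dates use two further degrees of freedom. Fix the model before any unblinded look at the data.

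The cost is a sentence or two and three of 36 error degrees of freedom. The covariates come from the allocation and the planned pre-race measurements. The downside is that nothing is gained, and a little precision is lost, if the covariates explain almost no variance.

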### Data storage

Data will be encoded in Access® for windows. Traceable participant data will be coded in a separate file, data used in analysis will not be traceable to the participant without the coding file. Data will be entered using the double data entry format.

## Discussion

This trial investigates a common procedure in elite athletes. Elite athletes run the risk of pulmonary inflammation and remodeling as a consequence of their frequent exercise, and thus increased ventilation in cold and dry environments [3,4,7]. Although inhalation of nebulized isotonic saline is commonplace, no study has ever investigated the safety or efficacy of this treatment.

Furthermore the pulmonary response to such an extreme performance has not been investigated in such detail, using not only spirometry and feeling of dyspnea, but also the FOT and EMG of breathing musculature.

There are some limitations to this study. First and foremost is the inclusion of the participants limited to elite skaters. Not all speed skaters however will show a substantial drop in FEV_1_ after exercise limiting the power of our study. In our experience however, at least 40% of elite speed skaters in the Netherlands will show a substantial drop in FEV_1_ after exercise, this is even higher than the percentage of American elite winter athletes experiencing EIB [2]. Furthermore the inclusion of the FOT and EMG measurements will allow more subtle evaluation of pulmonary function, not disrupted by forced breathing [9-11]. We will be able to analyze the smaller airways using the extensive pulmonary function measurements, however we preferred to also assess the damage to pulmonary parenchyma using Clara Cell protein (CC16) [18]. We believe however that analyzing CC16 in serum would have severely hampered the inclusion rate of the participants.

## Trial status

The trial is currently enrolling participants and collects data on three separate dates; all test dates will be official races, approved by the Royal Dutch Skating organization (http://www.knsb.nl). The first test date will be 21 December 2012. The second test date is planned in February 2013. A third test date will be added in the fall of 2013. Data analysis is expected to be completed in December 2013.

## Abbreviations

CCMO: Centrale Commissie voor Mensgebonden Onderzoek; EIB: Exercise-induced bronchoconstriction; EMG: Electromyography; FOT: Forced oscillation technique; RTPO: Regionaal Toetsingsorgaan voor Persoonsgebonden Onderzoek; VAS: Visual analogue scale; WADA: World anti-doping agency
